##### DSKI questionnaire score

The DSKI consists of 12 items examining the deficiency syndrome of the kidney [13]. Each item is rated on a three-point symptom scale (0 none, 1 average, and 2 severe) and the total score is used. The change of the DSKI score between randomization (visit 2) and after treatment (visit 5) will be calculated.

### Health-related quality of life status questionnaire

The EQ-5D is an outcome measurement that is widely used to assess quality of life in patients with osteoporosis [14], and is being used in this trial. This tool contains a five-item description section and a visual analog scale (EQ-VAS) [15]. The five-item description section includes questions on mobility, self-care, usual activity, pain and discomfort, and anxiety and depression. There are three possible responses to each item (no problems, some problems, and severe problems). The participants indicate their present health status by checking the most appropriate score for each of the five items. The EQ-VAS is a self-recorded health score for which the best imaginable health condition is 100 points and the worst is 0 points. The change in the score for each item of the EQ-5D between randomization (visit 2) and after treatment (visit 5) will be measured.

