## Methods/Design

### Objective

The primary aim of this study is to determine if treatment with BHH10 for 12 weeks results in a greater increase in BMD at L1–4 than those who receive a placebo. The secondary outcomes are:any significant differences in femoral BMD, bone turnover marker levels, DSKI, and EQ-5D score in the group receiving BHH10 compared to the group receiving the placebo after 12 weeks of treatmentto determine if there is a causal relationship between the primary outcome and the DSKI or EQ-5D scorewhether BHH10 is a safe treatment based on laboratory parameters, vital signs, and electrocardiography (ECG).

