#### Secondary outcome measurements

##### Femoral BMD

The change in femoral BMD between at baseline (visit 1) and after treatment (visit 5) will be calculated using the lowest values at the femoral neck and total hip.

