### Statistical analysis

The analysis data set will consist of an intention-to-treat data set, a per protocol (PP) data set, and a safety data set. The intention-to-treat data set will include all subjects assigned to each group. The PP data set will include only participants who adhered to the study protocol and completed the clinical study. The minimum compliance rate for participants taking the investigational drugs in the PP data set is 80%. The safety data set will include any participants who were randomly assigned to and received at least one dose of the investigational drug. The intention-to-treat analysis will be the primary analysis and will be compared with the PP analysis in a sensitivity analysis. The last observation carried forward method will be used to manage missing data.

For the descriptive analysis, the two-sample Student’s *t*-test or Wilcoxon rank sum test will be used for continuous data and the chi-squared test or Fisher’s exact test will be used for categorical data depending on whether the data are normally distributed or skewed.

For the confirmatory analysis, the primary efficacy endpoint, the change in BMD at the lumbar spine (L1–4) between baseline and 12 weeks, will be evaluated using Student’s *t*-test or the Wilcoxon rank sum test. The secondary endpoints will be evaluated using Student’s *t*-test or the Wilcoxon rank sum test for continuous data or the chi-squared test or Fisher’s exact test for categorical data. We will perform a regression analysis to examine the causal relationship between the DSKI, EQ-5D, and the primary outcome. All statistical analyses will be performed by a statistician blinded to treatment allocation using SAS (version 9.4, SAS Institute Inc., Cary, NC, USA). A significance level of 5% will be used.

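### The EQ-5D outcome is defined item by item, while the objective and the regression each need one EQ-5D score that the article never names

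*Protocol article*

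**What the plan says.** All references are to the protocol article.

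- **Health-related quality of life status questionnaire.** The EQ-5D is described as five items, each with three possible answers, plus the EQ-VAS. Of the latter it says: "The EQ-VAS is a self-recorded health score for which the best imaginable health condition is 100 points and the worst is 0 points". The outcome is then fixed as follows: "The change in the score for each item of the EQ-5D between randomization (visit 2) and after treatment (visit 5) will be measured". No index, sum or other summary of the five items is named.
- **Objective.** The secondary aim is "any significant differences in femoral BMD, bone turnover marker levels, DSKI, and EQ-5D score in the group receiving BHH10" against placebo. The EQ-5D score is singular here, as it is in the Abstract and the Background. A further aim relates the primary outcome to the DSKI or EQ-5D score.
- **DSKI questionnaire score.** For this instrument, also built from three-level items, the article does fix a total score.
- **Statistical analysis.** Secondary endpoints are compared by t-test or Wilcoxon test if continuous, and by chi-squared or Fisher test if categorical. A regression involves the DSKI, EQ-5D and the primary outcome. The general rule is: "A significance level of 5% will be used". No order or adjustment is given for the secondary tests.

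**The concern.** Two statements about the same outcome do not fit together. The aim asks whether the groups differ on one score; the definition supplies a separate change for each item. Five item results can point in different directions, and nothing says how they would be combined into an answer. The text also leaves open whether an item change counts as continuous or categorical, so the test for it is not settled either.

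The regression has the same gap with more room for choice. It needs one EQ-5D variable, and the text offers several candidates without picking one. If the pick is made once group results are visible, the reported association can follow the data.

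At stake is a clear, pre-stated answer to one secondary question. The lumbar spine result is not at stake.

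**Working it through.** **1. The plan's own figures.** The article gives no count of secondary tests and no overall error rate, so there is no figure on this point to reproduce. Its one computed figure is the sample size, from a difference of 0.047, an SD of 0.097, 5% (taken as two-sided) and 80% power:

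2 × (0.097 × (1.960 + 0.842) / 0.047)² = 66.9, so 67 per group against 66 stated; 67 / 0.80 = 83.75, so 84 per group and 168 in total.

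It rests on lumbar spine BMD only and does not depend on how the EQ-5D is scored.

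**2. What an item change can show.** With three levels per item, the change from visit 2 to visit 5 is −2, −1, 0, +1 or +2: five values. The five items together give 3⁵ = 243 possible answer profiles, which an index would place on one scale.

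**3. Candidates for the regression variable.** Five item changes and the EQ-VAS make 5 + 1 = 6, before any summary that the article does not define.

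**4. Count of secondary tests,** from the outcome sections:

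| Outcome | As written | With one index |
|---|---|---|
| Femoral BMD ("will be calculated using the lowest values at the femoral neck and total hip", read as one value) | 1 | 1 |
| DSKI total | 1 | 1 |
| EQ-5D five items | 5 | 1 |
| EQ-VAS | 1 | 1 |
| Bone turnover markers (3 formation, 2 resorption) | 5 | 5 |
| **Total** | **13** | **9** |

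The article does not say whether its item-level rule covers the EQ-VAS. Without it the totals are 12 and 8.

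**5. Chance of at least one false positive** with no true effect and 5% per test. If independent, it is 1 − 0.95^k:

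- k = 13: 48.7%; k = 12: 46.0%
- k = 9: 37.0%; k = 8: 33.7%

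With an assumed common correlation between all tests (simulated):

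| Correlation | 13 tests | 9 tests |
|---|---|---|
| 0.3 | 42% | 32% |
| 0.5 | 33% | 27% |
| 0.7 | 24% | 20% |

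The item split adds four tests. Most of the multiplicity comes from the other secondary outcomes and would remain after the split is removed.

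**The case against.** The strongest reply is that this is a condensed article on a phase II trial. Unadjusted secondary tests are usual at that stage, and a value set or scoring algorithm normally sits in the analysis plan, which is not shown. That stands for multiplicity and for scoring detail. It does not remove the inconsistency: the article states an item-level rule, and an analysis plan built on an index would depart from it.

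A reader might infer four stronger things that the text does not support:

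- **That there is no overall quality-of-life score.** The EQ-VAS is one. What is missing is a summary of the five-item section.
- **That the secondary tests are declared confirmatory.** In the Statistical analysis section that word is tied to the change in lumbar spine BMD. The secondary endpoints follow in the same paragraph, which is loose, but nothing gives them that status.
- **That about half of such trials would yield a false secondary claim.** The 49% needs 13 independent tests. Outcomes from the same women are plausibly correlated, and the wording of the aim introduces a list of comparisons, not a rule that one positive result means success.
- **That item changes will be mostly zero, so the tests are known to be weak.** The article gives no EQ-5D response distribution, expected change or power. Low sensitivity is plausible from the coarse scale but not shown.

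**Conclusion.** The point holds as a minor one. The item-level definition conflicts with the single score in the objective and with the single EQ-5D variable in the regression; these sections need to be reconciled.

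The direct consequence is five coarse results plus EQ-VAS where one answer was promised, and a regression variable that can be chosen late. The multiplicity effect is secondary: 13 tests become 9, and 49% becomes 37% under independence, which are upper-end figures once positive correlation is allowed for. This rests on three assumptions: EQ-VAS is tested separately, femoral BMD is one test, and testing is two-sided. The primary endpoint and the sample size are unaffected.

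**What to change.** Before unblinding:

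1. Make one EQ-5D-3L index score the EQ-5D endpoint, with the value set named in the analysis plan.
2. Use the same index as the EQ-5D variable in the regression.
3. State EQ-VAS as a separate score.
4. Compare index and EQ-VAS between groups by ANCOVA on the visit-2 value, which is already collected. This uses the baseline information that a test on raw change uses less efficiently.
5. Report the five items descriptively by group and visit.

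The cost is a few sentences and a scoring table, with no new data. The downside is that no formal item-level tests remain.

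On timing: recruitment ended in April 2018 and treatment lasts 12 weeks, so last visits would fall around July 2018, before the article's publication in September 2018. The article does not say whether the blind has been broken. If it has, the choice of score should be reported as made afterwards.

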### Bone turnover markers

Levels of bone formation markers (bone-specific alkaline phosphatase, insulin-like growth factor-1, and osteocalcin) and bone resorption markers (C-telopeptide and N-telopeptide) will be observed at baseline (visit 1) and after treatment (visit 5). The change in these markers will be measured.

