### Sample size

The primary null hypothesis of this study is that there is no difference in the change in BMD at the lumbar spine (L1–4) between the BHH10 and placebo groups after 12 weeks of treatment. In view of the results of a similar study of herbal medicine in postmenopausal women with osteoporosis [16], a mean difference of 0.047 ± 0.097 between the experimental group and control group was assumed. With a 5% significance level and a power of 80%, it was calculated that a sample size of 66 patients per group would be necessary. Allowing for a dropout rate of 20%, a sample size of 168 participants (84 in each group) has been included.

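### Bone turnover markers are compared as an unadjusted plain change, which discards the baseline value and may cost power on these secondary endpoints

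*Protocol article*

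**What the plan says.** In the protocol article, the section Bone turnover markers lists three formation markers and two resorption markers, observed at visits 1 and 5. It then says "The change in these markers will be measured". It names no scale: not absolute, percentage or logarithmic.

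The Statistical analysis section fixes the test: "The secondary endpoints will be evaluated using Student’s *t*-test or the Wilcoxon rank sum test for continuous data". No covariate is mentioned. The preceding paragraph, on descriptive analysis, makes the choice of test turn on distribution: "depending on whether the data are normally distributed or skewed". That rule is not repeated for the secondary endpoints, though it presumably carries over.

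The article gives no SD, skewness, baseline-to-follow-up correlation or expected effect for any marker. The Sample size section concerns lumbar spine BMD only.

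**The concern.** The article uses the same word, change, for BMD and for the kidney-deficiency questionnaire score, where it plainly means a difference. Read the same way for serum or urine markers, it means visit 5 minus visit 1 in concentration units.

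Two separate things may then be lost.

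- **Baseline information.** Neither permitted test uses the baseline value beyond subtracting it. Subtraction is efficient only when the correlation between the two visits is close to 1.
- **Scale.** If a treatment lowers a marker by a fixed percentage, the raw fall is large in a woman with high turnover and small in one with low turnover. The spread of raw changes then grows with baseline, and the contrast between arms is estimated less precisely. Wilcoxon limits the pull of extreme values but still ranks raw differences.

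At stake is the trial's ability to detect an effect on bone biochemistry. The Discussion presents the markers as a way to explore possible advantages of BHH10, and the trial is meant to prepare for phase III.

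**Working it through.** **The plan's own figure.** The sample size rests on a BMD difference of 0.047 and an SD of 0.097: "With a 5% significance level and a power of 80"%. Sidedness is not stated, but a null that "there is no difference in the change in BMD" points to a two-sided test.

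n per group = 2 × (1.960 + 0.842)² × (0.097/0.047)² = 2 × 7.85 × 4.26 ≈ 66.9, so 67 against the stated 66. Dividing by 0.8 for dropout gives 67/0.8 = 83.75, or 84 as stated. The figure reproduces closely. It does not involve the markers and only supplies a realistic number of completers: 84 × 0.8 ≈ 67 per arm.

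**What baseline adjustment does.** Let σ be the log-scale SD and ρ the log-scale correlation between visits, with equal variances at both visits.

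- Variance of log change: 2σ²(1 − ρ)
- Residual variance after adjusting for log baseline: σ²(1 − ρ²)
- Ratio of the second to the first: (1 + ρ)/2, which is 0.80 at ρ = 0.6 and 0.90 at ρ = 0.8

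The same ratio holds on any scale where the relation is linear, so this part does not depend on skewness.

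**Worked example (assumed inputs).** Baseline CV 60%, ρ = 0.6, a 20% fall, 67 per arm, two-sided 5%.

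- σ = √ln(1 + 0.6²) = 0.5545; effect = −ln(0.8) = 0.2231; √(2/67) = 0.1728
- Log change: SE = 0.5545 × √0.8 × 0.1728 = 0.0857; power ≈ Φ(0.2231/0.0857 − 1.96) ≈ 74%
- With log baseline: SE = 0.5545 × √0.64 × 0.1728 = 0.0766; power ≈ Φ(0.2231/0.0766 − 1.96) ≈ 83%

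Adjustment is therefore worth about 9 points here.

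**Simulation of all methods.** Bivariate lognormal values, 67 per arm, 8,000 trials per row. Entries are power in percent.

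| CV, ρ, fall | Raw change, t-test | Raw change, Wilcoxon | Raw change + baseline | Log change, t-test | Log change + log baseline |
|---|---|---|---|---|---|
| 60%, 0.6, 20% | 58.0 | 62.8 | 73.4 | 73.0 | 81.5 |
| 40%, 0.6, 15% | 69.2 | 69.9 | 82.2 | 77.4 | 85.7 |
| 60%, 0.8, 15% | 60.4 | 65.6 | 69.6 | 75.7 | 79.8 |
| 40%, 0.8, 15% | 92.5 | 93.5 | 96.3 | 96.6 | 97.7 |
| 25%, 0.8, 10% | 95.6 | 95.5 | 97.9 | 97.5 | 98.4 |
| 60%, 0.6, none | 5.0 | 5.0 | 4.9 | 5.3 | 5.4 |

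In the first three rows, adding log baseline to log change gains 8.5, 8.3 and 4.1 points. The full log model gains 18.7, 15.8 and 14.2 points over raw Wilcoxon. Across separate simulation runs these ranges were about 3 to 9 and 13 to 20. In rows four and five power is already above 90%, and the full model gains only 4.2 and 2.9 points over Wilcoxon. The last row shows type I error near 5% for every method.

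**The opposite assumption.** Roughly normal markers (mean 1, values floored at 0.05), an additive fall, ρ = 0.6, 67 per arm:

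| CV, fall (fraction of mean) | Raw change, t-test | Raw change, Wilcoxon | Raw change + baseline | Log change, t-test | Log change + log baseline |
|---|---|---|---|---|---|
| 40%, 0.15 | 66.9 | 64.8 | 76.3 | 58.1 | 65.7 |
| 30%, 0.12 | 73.0 | 71.0 | 81.8 | 68.4 | 75.9 |
| 25%, 0.10 | 72.4 | 70.4 | 81.4 | 71.1 | 78.5 |

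Here the log scale loses about 3 to 11 points against baseline-adjusted raw change. Adjustment on a given scale still helps in every row. Against the planned unadjusted raw t-test, the log model ranges from about 1 point worse to 6 points better.

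**The case against.** The strongest objection is that the article never says raw. A condensed article may leave the scale of five laboratory markers to the full protocol or analysis plan, which are not shown. This stands as far as scale goes: a simple difference is only the most natural reading. It does not dispose of the tests, which the article names without a covariate.

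The second objection is that skewness, proportional response, CVs and correlations are all assumed, and a lognormal simulation favours the log scale by construction. This also stands, and the second table shows the ranking of scales reversing. The benefit of baseline adjustment does not rest on that assumption.

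The third is that the largest contrast, 58.0% against 81.5%, mixes change of scale with adjustment and uses the weaker of the two permitted tests. This is fair, so the gains are given separately and against Wilcoxon.

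A reader might go further and infer any of the following, none of which the documents support:

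- **Women with high baseline values dominate the comparison.** That is mainly a t-test problem. The article allows Wilcoxon, and ranks bound any one woman's influence.
- **The result is biased by how many high-turnover women fall in each arm.** Allocation is randomized, and type I error stays near 5%. The loss is in precision.
- **Entry leaves baseline turnover unrestricted.** No marker cut-off is set, but the Exclusion criteria remove alkaline phosphatase above twice the upper limit, other metabolic bone disease, hypercalcemia, and osteoporosis drugs within 3 months or injections within 6 months.

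**Conclusion.** The point holds as a minor one. As written, the marker endpoints are a plain change compared without adjustment, and a baseline value already in hand goes unused as a covariate.

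The size depends on assumptions outside the documents. With lognormal markers, a proportional fall of 15-20% and a CV of 40-60%, adjustment adds about 3 to 9 points to an analysis of log change. The full log model adds about 13 to 20 points over raw Wilcoxon, unless power is already high. At a CV of 25% little is lost.

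Only the sensitivity of secondary endpoints is affected. Validity, type I error, the sample size and the primary BMD analysis are untouched. The documents do not support saying that the trial will miss a real marker effect, since they give no marker distribution or expected response.

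**What to change.** Before unblinding, pre-specify for each of the five markers a linear model of log(visit 5/visit 1) on treatment, with log baseline as covariate. Report the treatment effect as a ratio of geometric means with a 95% CI, and keep the raw change as descriptive.

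The change is to the wording of the analysis plan only, with no new samples, visits or assays. The price is some loss of power against baseline-adjusted raw change if a marker proves roughly normal with an additive effect. The scale should therefore be fixed in advance, not chosen after the arms have been compared.

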### Sample size

The primary null hypothesis of this study is that there is no difference in the change in BMD at the lumbar spine (L1–4) between the BHH10 and placebo groups after 12 weeks of treatment. In view of the results of a similar study of herbal medicine in postmenopausal women with osteoporosis [16], a mean difference of 0.047 ± 0.097 between the experimental group and control group was assumed. With a 5% significance level and a power of 80%, it was calculated that a sample size of 66 patients per group would be necessary. Allowing for a dropout rate of 20%, a sample size of 168 participants (84 in each group) has been included.

### Criteria for withdrawal

Violation of inclusion or exclusion criteriaAn adverse event or a serious adverse eventAn acute reaction (allergy or anaphylaxis) to the investigational drugSystemic disease not detected at the time of screeningLess than 70% compliance with the investigational treatment at the final evaluationUnsatisfactory treatment effect during the trialTaking of other medication that could affect the results of the study without consulting the researchersNon-compliance with the requirements of the trialLoss to follow-upWorsening of disease or accidental concomitant diseaseContinuation in the trial is deemed inappropriate by the researchers

### Data management

Researchers who have read and understood the standard operating procedures will obtain written consent and collect and manage the study data from the participants, who will be given ongoing encouragement to complete the study. They are telephoned in advanced of each visit and the importance of taking the investigational drugs at the correct times is reinforced. If a participant needs to be withdrawn from the study, the scheduled tests are still performed at the final study visit if the participant is agreeable. If a follow-up investigation is required, researchers will contact the participant by telephone as necessary. After the end of the trial, data entry will be by double entry, and matching will be conducted after inconsistent data has been reviewed. When the data are matched, a data clarification form will be completed and validated. The resolution will be reflected in the data, and medical coding will be performed using MedDRA (version 17.0).

### Statistical analysis

The analysis data set will consist of an intention-to-treat data set, a per protocol (PP) data set, and a safety data set. The intention-to-treat data set will include all subjects assigned to each group. The PP data set will include only participants who adhered to the study protocol and completed the clinical study. The minimum compliance rate for participants taking the investigational drugs in the PP data set is 80%. The safety data set will include any participants who were randomly assigned to and received at least one dose of the investigational drug. The intention-to-treat analysis will be the primary analysis and will be compared with the PP analysis in a sensitivity analysis. The last observation carried forward method will be used to manage missing data.

For the descriptive analysis, the two-sample Student’s *t*-test or Wilcoxon rank sum test will be used for continuous data and the chi-squared test or Fisher’s exact test will be used for categorical data depending on whether the data are normally distributed or skewed.

For the confirmatory analysis, the primary efficacy endpoint, the change in BMD at the lumbar spine (L1–4) between baseline and 12 weeks, will be evaluated using Student’s *t*-test or the Wilcoxon rank sum test. The secondary endpoints will be evaluated using Student’s *t*-test or the Wilcoxon rank sum test for continuous data or the chi-squared test or Fisher’s exact test for categorical data. We will perform a regression analysis to examine the causal relationship between the DSKI, EQ-5D, and the primary outcome. All statistical analyses will be performed by a statistician blinded to treatment allocation using SAS (version 9.4, SAS Institute Inc., Cary, NC, USA). A significance level of 5% will be used.

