#### Study plan

This study will be conducted in two phases (Fig. 1):Screening (2 weeks): Trained researchers in the hospital will explain this trial to and seek written informed consent from potentially eligible patients. Patients who agree to participate in the study will undergo BMD measurements, laboratory investigations, and an ECG. The results of these tests will be conveyed by telephone and patients who meet the inclusion criteria will be randomized within 2 weeks after the screening visit.Treatment (12 weeks): On the second visit, patients will be randomly assigned to one of the two groups (the BHH10 group or the placebo group) and supplied with their allocated investigational drugs after completing the DSKI and EQ-5D questionnaires. Participants will take two tablets of BHH10 or placebo three times daily for 12 weeks. Additional visits will be made at monthly intervals during the 12 weeks of treatment. A total of four visits will be made during the treatment period. A blood test will be conducted 8 weeks after randomization (visit 4). BMD measurements, blood and urine tests, and an ECG will be performed 12 weeks after randomization (visit 5).

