#### Primary outcome measurement

The primary outcome will be the change in BMD at the lumbar spine (L1–4) between baseline (visit 1) and 12 weeks after randomization (visit 5). BMD will be examined by dual-energy X-ray absorptiometry. Both participating institutions use the same type of X-ray machine (Lunar Prodigy, GE Medical Systems Lunar, Madison, WI, USA).

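### The stated sensitivity analysis, intention-to-treat against per-protocol, changes the population and the missing-data handling together, so it cannot isolate whether the primary result depends on the missing-data assumption

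*Protocol article*

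**What the plan says.** All of the following is in the Protocol article.

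- **Primary and sensitivity analysis** (Statistical analysis): "The intention-to-treat analysis will be the primary analysis and will be compared with the PP analysis in a sensitivity analysis".
- **Intention-to-treat (ITT) set** (same section): "The intention-to-treat data set will include all subjects assigned to each group".
- **PP set** (same section): "The PP data set will include only participants who adhered to the study protocol and completed the clinical study". A tablet threshold is added: "The minimum compliance rate for participants taking the investigational drugs in the PP data set is 80" per cent.
- **Missing data** (same section): "The last observation carried forward method will be used to manage missing data".
- **BMD timing**: Primary outcome measurement defines the endpoint as the change from visit 1 to visit 5. Study plan places the only on-treatment scan at the end: "BMD measurements, blood and urine tests, and an ECG will be performed 12 weeks after randomization (visit 5"). The visit 4 assessment it describes is a blood test.
- **Ways out of the trial** (Criteria for withdrawal): the list includes adverse events, insufficient effect, worsening disease, and compliance under 70% as judged at the final evaluation.
- **Tests after withdrawal** (Data management), subject to the woman's consent: "If a participant needs to be withdrawn from the study, the scheduled tests are still performed at the final study visit if the participant is" [willing].

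**The concern.** A sensitivity analysis should keep the question fixed and vary one assumption behind the answer. The ITT-against-PP comparison does not do that. Moving from ITT to PP drops the women whose value was carried forward. It also drops women who have a real week-12 value but fell short on adherence or were withdrawn. What remains is the effect in adherent completers, a different question in a group formed after randomisation.

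Several routes out of the PP set can depend on arm and outcome: adverse events, insufficient effect and worsening disease. The two arms of the PP set then need not be comparable.

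At stake is how the trial's result will be interpreted. The sample size allows for 20% dropout, so the treatment of missing week-12 values could matter. A PP result that agrees may be taken as support when both analyses lean the same way. One that disagrees gives no indication of why.

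**Working it through.** **Inputs.** From Sample size: difference 0.047, SD 0.097, 5% level (taken as two-sided), 80% power, 66 per group, 20% dropout, 84 per group. The dropout mechanisms below are assumptions; the documents give none.

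**1. The plan's own figure.** n per group = 2 × (1.960 + 0.842)² × 0.097² / 0.047² = 66.9, so 67 against the stated 66. Then 67 / 0.8 = 83.75, so 84 per group and 168 in total. This agrees within one woman per group and supports reading 0.097 as the SD of the change.

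**2. Who is in which analysis.**

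| Woman | ITT | PP |
|---|---|---|
| Completed, adherent, scanned | observed change | observed change |
| Completed, scanned, compliance under 80% | observed change | excluded |
| Withdrawn, agreed to final tests | observed change, if the scan is used | excluded |
| No week-12 scan | baseline carried forward, change = 0 | excluded |

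The zero in the last row follows because no scan is described between visits 1 and 5. Only that row concerns missing data, but the PP set removes the last three rows together.

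**3. A difference can arise with no adherence effect.** Suppose dropout is unrelated to outcome, a share q is missing in each arm, and the true effect is 0.047. The expected ITT difference under zero-change LOCF is 0.047 × (1 − q): 0.042 at q = 0.1, 0.038 at 0.2 and 0.033 at 0.3. The expected PP difference stays at 0.047. Selective dropout or a real adherence effect could also produce such a gap, and the comparison cannot tell these causes apart.

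**4. Agreement can arise when both are wrong.** Simulation: 84 per arm, SD 0.097, no true effect, 4,000 trials. BHH10 women with poorer change are likelier to drop out (assumed log-odds slope per SD of change); placebo dropout is unrelated to outcome. About 20% are missing on placebo, and 24% (slope 1) or 27% (slope 1.5) on BHH10. Here PP differs from ITT only by omitting unscanned women.

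| Slope | ITT-LOCF difference | PP difference | ITT falsely favours BHH10 | PP falsely favours BHH10 | Same significance call |
|---|---|---|---|---|---|
| 0 | 0.000 | 0.000 | 2.2% | 2.2% | 99.7% |
| 1 | 0.015 | 0.020 | 21% | 22% | 98% |
| 1.5 | 0.021 | 0.029 | 40% | 42% | 97% |

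The nominal rate in that direction is 2.5%. Agreement includes trials where neither test is significant, so consider the false positives alone at slope 1. ITT is falsely positive in 20.95% of trials, PP in 21.95%, and the two disagree in 2.0%. ITT alone is then positive in at most (2.0 − 1.0) / 2 = 0.5%. At least 20.45 / 20.95 = 98% of the false ITT positives would be matched by PP.

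**5. Size of selection in the PP test.** Let a share f of BHH10 women leave the PP set, with a change k SDs worse than that of retained women, and let placebo lose the same share at random. With no true effect:

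- shift = f × k × 0.097
- n per arm = 84 × (1 − f)
- SE = 0.097 × √(2/n)
- rejection rate = P(|Z + shift/SE| > 1.96)

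| f | k | Shift | Share of 0.047 | n per arm | SE | Rejection |
|---|---|---|---|---|---|---|
| 0.2 | 0.25 | 0.0049 | 10% | 67.2 | 0.0167 | 6.0% |
| 0.2 | 0.5 | 0.0097 | 21% | 67.2 | 0.0167 | 8.9% |
| 0.3 | 0.25 | 0.0073 | 15% | 58.8 | 0.0179 | 6.9% |
| 0.3 | 0.5 | 0.0146 | 31% | 58.8 | 0.0179 | 12.9% |

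If placebo loses nobody (n = 84 there), the range becomes 6.1 to 14.3%.

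**The case against.** The strongest reply is that ITT as primary with PP alongside is conventional in a superiority trial. PP decides nothing here, and an article condenses a fuller protocol. All of that stands. It limits the point to the role the text gives to the comparison; it does not make the comparison suited to that role.

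Four stronger readings are tempting, and the documents do not support them.

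- **That no other sensitivity analysis exists.** The analysis plan and full protocol are not shown and may contain others. The point concerns the one stated here.
- **That the PP set drops exactly the women with missing week-12 BMD.** It also drops scanned women below 80% compliance and withdrawn women who agreed to final tests. Those tests also mean that the 20% allowance for dropout need not equal the share of missing scans.
- **That the comparison says nothing about LOCF.** PP is limited to completers and so largely removes carried-forward values, as step 3 shows. The trouble is that this change is mixed with adherence selection.
- **That the trial's false-positive rate is 6 to 13%.** That range belongs to the PP test under assumed selection in one arm.

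It is also fair to say that the 21 to 42% rates in step 4 reflect informative dropout and zero-change LOCF at least as much as PP. They are used here only to show that the two analyses can err together. With dropout unrelated to outcome and no effect, both keep about their nominal error.

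**Conclusion.** The point holds as a criticism of a stated method. Because the comparison alters the population and the missing-data handling at once, agreement is weak support for the primary result and disagreement has no identifiable cause.

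No single size can be given. Under the assumptions shown, selection shifts the PP difference by 0.005 to 0.015, or 10 to 31% of the planned 0.047. LOCF alone can open a gap of 0.047 − 0.038 = 0.009 at 20% missing. These figures rest on assumed dropout mechanisms, on 0.097 being the SD of the change, and on there being no BMD scan between visits 1 and 5. That last reading comes from the text, since the schedule figure is not shown. The correction is worth making. The choice of ITT as primary is not in question.

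**What to change.** Before unblinding, define the sensitivity analysis of the primary endpoint on all randomised women. Use every week-12 lumbar BMD obtained, including those taken after withdrawal, and vary only the assumption about the values still missing. One suitable form is multiple imputation with a shift (delta) applied separately by arm, reporting the shift at which the primary conclusion changes (a tipping point).

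Keep the PP analysis, label it supplementary (effect in adherent completers), and do not cite it as evidence that the primary result is robust. If the analysis plan already contains such an analysis, it is enough to give that one the sensitivity role and relabel PP.

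The cost is a few lines of text and standard code in the SAS version already specified. No new data are needed. The downside is one more analysis to report.
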